**Fig. 1 Fig1:**
[figure not shown]
Study flow chart. The flow chart of enrolment, allocation, intervention and assessment. *Intervention Group has ten additional appointments for systematic orientation for a continuous global simulation at home and ten home visits

Sample size: the sample size was calculated on the basis of the results of many studies that assessed improvement of motor and mental development or cognitive or language acquisitions. All these studies obtained minimum scores 20% higher after early intervention. For a 5% level of significance and a statistical power of 80%, a sample size of 84 patients will be required to detect a 3-point between-group difference in development scores [20, 24–26]. The allocation of the subjects will be perfomed until the complete calculated sample size based on the number of premature infants who survive until hospital discharge. A number of 20% (number 16) will be added, considering possible loss or death during the follow-up. Total sample size will be 100 preterm infants.

Recruitment: strategies for achieving adequate participant enrolment to reach target sample size will be: to establish a link between the research team and mother and father of each of the subjects included, regardless of the group allocated since randomization. Weekly meetings are performed during NICU stay.

A telephone number is available twenty-four for all questions after discharge and during the follow up. This mobile phone stays each day with a researcher’s member on call to resolve doubts with clarity and security. A prior scheduling of home visits and office appointments is done continuously during the recruitment and assessment according the objectives.

Assignment of interventions: Monitoring the progress of this research is fundamental for assuring that all activities will be achieving stated milestones. The selection of adequate method for generating the randomization sequence is important for result measurements. We have used the research randomizer program available at www.randomizer.org [23].

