Simple randomization method for allocation: computer-generated random numbers for each 5 participants determines the allocation group. The trial is monitored during the process to have a balance in the number of subjects on each arm over time, eg, twins, triplets; they will be allocated for the same group. We have not stratification by gender, gestational age, or any other variable. In neonatal period, preterm infants will be sequentially randomized when they completed 48 h after birth. Randomization is performed by researchers that will not be responsible for any intervention, nor outcome measures of parental bond, motor and cognitive outcomes. The same researchers will register all neonatal data, discharge variables and the follow-up data, during the appointments (not blinded). During the NICU stay period, the nursing and the medical staff were informed that participating infants would receive an active intervention by the mothers depending on group allocation (not blinded). The data analysts, outcome assessors and the multidisciplinary team working in the institutional follow up clinic will be blinded.

The allocation of the subjects will be maintained until the complete sample size calculation. Both arms are routinely candidates for outpatient institutional follow-up clinic.

Data collection, management and analysis are being presented according checklist [23].

Data collection: Clinical morbidities and identification data were prospectively collected in duplicate during hospital stay until hospital discharge for the two independent researchers.

Both groups have all data obtained during regular appointments at the outpatient follow up clinic masked for allocation of patient groups. All variables will have double data entry in data record center storage.

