Neonatal variables include maternal and perinatal characteristics and short-term outcomes. The maternal characteristics are: age, parity, number of prenatal visits, gestational diabetes, chronic hypertension or preeclampsia, chorioamnionitis or urinary tract infection, household income and educational level. The neonatal variables are: gender, type of delivery, 1 and 5 min Apgar scores, surfactant use (at least one dose), antenatal corticosteroid use, gender, gestational age (evaluated by the last menstrual period and confirmed by an early obstetrical ultrasound and neonatal clinical examination), birth weight and small-for-gestational-age status (defined as a birth weight below the 10th percentile), and the Neonatal Acute Physiology and Perinatal Extension II (SNAPPE II) score. The presence of Respiratory Distress Syndrome, bronchopulmonary dysplasia, apnea of prematurity, early or late onset sepsis as confirmed using positive blood cultures, meningitis, necrotizing enterocolitis, patent ductus arteriosus, perintraventricular hemorrhage and periventricular leukomalacia (as determined by brain ultrasound and confirmed using magnetic resonance imaging during the follow-up period within the first 12 months of corrected age), retinopathy of prematurity and universal neonatal hearing screening evaluation (otoacoustic emissions- OAE) during the neonatal period and BERA until six months of corrected age have been also assessed in both arms.

During the follow up three pediatrician/neonatologist will be evaluating monthly, until 6 months of corrected age (CA), bimonthly from 7 up to 12 months corrected age, and every 3 months thereafter until age 24 months, according to routine hospital practice all very low birth weight infants of the study. According randomization conventional group will have standard care of a traditional follow up clinic taking care of the demands according to their necessity and the intervention group, will receive orientation for a continuous global simulation at home besides the usual appointments to the follow up clinic (as previously presented), monthly in the first semester corrected age and bimonthly in the second semester until 12 months corrected age and every 3 months thereafter until age 24 months corrected age. Multidisciplinary team will participate of these activities all the time. All these data can be found in the protocol.

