Growth velocity will be registered in the reference curves, using the two computers with an appropriate statistical program for nutritional assessment (ANTHRO). There are two nutritionists to perform the growth evaluations in the exact moments in each group (blinded to which group the child was previously allocated). In the Intervention Group there will be a Nutritionist that will make home visits with the team to reinforce breastfeeding practices. The research team is using a check list during the home visits to the Intervention Group; home visits should be done at least two more researchers.

Statistical methods: All analyses will be performed in the PASW Statistics® for Windows, Version 18.0 software environment (Chicago, IL: SPSS Inc. Released 2009). Qualitative variables will be expressed as absolute and relative frequencies. Pearson chi-square test will be employed to determine the association between categorical variables, with adjusted residuals in case of statistical significance.

Symmetrically distributed continuous variables will be described as means and standard deviations, while asymmetrical distributed categorical variables being described as medians and interquartile ranges. Fisher’s exact test for comparison of categorical variables and Student’s t or the Mann–Whitney tests for comparisons of symmetrically distributed quantitative variables and asymmetrically distributed variables, respectively will be used. Subgroup and any additional analyses will be performed to adjust for social status, maternal age and some preterm’s neonatal conditions associated with poor neurodevelopment outcome.

Monitoring: There are five researchers to monitor data without competing interest. All researchers are independent from sponsor. Data are continuously monitored during the study. The teaching activities and educational programs for the families will be the focus of our research group throughout the study and if some adverse events occur, will be reported. Previous published study showed that the intervention during NICU stay is safe; the 10 additional appointments and 10 home visits will check the intervention safety [23].

Table 2 summarizes the project framework regarding specific objectives, outcomes and period of activities.

**Table 2 Tab2:** Project Framework: specific objectives, outcomes and period of activities

Specific Objectives	Outcomes	Period acticvities
Objective 1:		

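### The tests named for the development scores ignore baseline variables already collected, and the additional adjusted analyses are not limited to variables fixed before randomisation

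*Protocol article*

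**What the plan says.** All references are to the Methods of the protocol article.

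- **Statistical methods, tests.** For quantitative variables the text names Student's t and Mann-Whitney "tests for comparisons of symmetrically distributed quantitative variables and asymmetrically distributed variables, respectively will be used". No covariate enters these tests.
- **Statistical methods, adjustment.** Adjustment is kept for subgroup and additional analyses, which are to "adjust for social status, maternal age and some preterm’s neonatal conditions associated with poor neurodevelopment outcome". The neonatal conditions are not named, and no time limit is set.
- **Simple randomization.** Infants are randomised on completing 48 hours of life. On stratification: "We have not stratification by gender, gestational age, or any other variable".
- **Data collection.** Gestational age, sex, birth weight, SNAPPE II, household income and maternal education are recorded. The same paragraph counts short-term outcomes among the neonatal variables and goes on to morbidities: "The presence of Respiratory Distress Syndrome, bronchopulmonary dysplasia, apnea of prematurity, early or late onset sepsis", followed by necrotizing enterocolitis, retinopathy and brain lesions.
- **Interventions.** The intervention is planned to start on the seventh day of life. Both arms receive kangaroo care and the breastfeeding policy; maternal massage is the in-hospital addition.
- **Sample size.** "a sample size of 84 patients will be required to detect a 3-point between-group difference in development scores". Then: "Total sample size will be 100 preterm infants".

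**The concern.** Two separate matters meet in one short paragraph.

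First, a small unstratified trial can end with arms that differ by chance in maturity, sex or family background. The tests named for the scores neither correct for that nor use the information in those variables, although the data are already in hand. The loss is precision, in a trial that has little to spare.

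Second, the phrase about neonatal conditions is open-ended. The trial records a mixture of variables fixed at birth and conditions that can develop after 48 hours, some of them during the intervention. If one of the latter were changed by the intervention, adjusting for it or subgrouping by it would no longer estimate the total effect of allocation. An unlisted set also leaves room to choose covariates after the data are seen.

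**Working it through.** **1. The plan's own figure.** Inputs from Sample size: a 3-point difference, 5% significance, 80% power, 84 infants, 16 added, 100 in total. For two equal arms, n per arm = 2(z_α + z_β)² SD² / 3². No SD is stated, so 84 cannot be reproduced directly. Solving backwards with 42 per arm:

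SD = 3 / [(1.960 + 0.842) × √(2/42)] = 4.9 (two-sided); 5.5 if one-sided.

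The total is a plain sum: 84 + 16 = 100.

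**2. Precision from baseline adjustment.** Let r be the multiple correlation of the baseline covariates with the score. Adjustment multiplies the residual variance by 1 − r², so 84 infants perform like 84/(1 − r²). The values of r are assumed.

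| r | 1 − r² | 84/(1 − r²) |
|---|---|---|
| 0.3 | 0.91 | 92 |
| 0.4 | 0.84 | 100 |
| 0.5 | 0.75 | 112 |

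The next table gives power for 3 points with 42 per arm (normal approximation, two-sided). R² runs from 0.1 to 0.4, somewhat beyond the range above (0.3² = 0.09 to 0.5² = 0.25). The SD of 4.9 is the implied value; 10 and 15 are assumed alternatives.

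| SD | Unadjusted | R² 0.1 | R² 0.2 | R² 0.3 | R² 0.4 |
|---|---|---|---|---|---|
| 4.9 | 80.1% | 84.1% | 88.0% | 91.8% | 95.2% |
| 10 | 27.9% | 30.5% | 33.6% | 37.6% | 42.7% |
| 15 | 14.8% | 16.0% | 17.5% | 19.4% | 21.9% |

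These figures treat infants as independent.

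**3. Chance imbalance.** With 42 per arm, the standard error of a standardised baseline difference is √(2/42) = 0.218. An imbalance of that size in a covariate correlated r with the score shifts the raw score difference by 0.218 × r × SD. At SD 4.9 this is 0.218 × 0.3 × 4.9 = 0.3 points to 0.218 × 0.5 × 4.9 = 0.5 points, against a target of 3. A covariate-adjusted model removes this shift to the extent that the relation is linear.

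**4. Timing of the recorded conditions.**

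- *Fixed by 48 hours:* gestational age, birth weight, sex, Apgar scores, maternal age, education and income.
- *Arising between 48 hours and day 7:* after randomisation but before the planned start, so unlikely to be changed by the intervention.
- *Able to arise later:* late-onset sepsis and bronchopulmonary dysplasia, for example.

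The adjustment phrase does not separate these groups.

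**5. Possible distortion of an additional analysis.** The part of the effect removed by adjusting for a later condition is roughly (points the condition costs) × (difference in its incidence between arms). With assumed values:

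- smallest: 5 × 0.05 = 0.25 points, or 0.25/3 = 8% of the target;
- largest: 10 × 0.15 = 1.5 points, or 1.5/3 = 50% of the target;
- if the intervention does not change the condition: about zero.

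A simulation gave the same pattern. It assumed a condition present in 33% of controls, costing 8 points and sharing an unmeasured cause with the score. A total effect of 3.7 became 2.7 after adjustment, and 4.1 became 2.6. With no effect on the condition, the estimate stayed at 3.0.

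**The case against.** The strongest reply is that an unadjusted comparison of randomised arms is valid, that allocation without stratification is acceptable, and that a condensed article may leave its covariate list to a fuller document. Most of this stands. The tests named are not wrong, and a missing list alone would not be a finding. What remains is that the article does commit to unadjusted tests and rules out stratification, when a more precise analysis is available from data already collected.

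It can also be said that the Statistical methods text gives general rules and does not single out a primary test. Table 2 lists numbers of infants in the normal range, which would be compared by chi-square or Fisher's test. That is fair: the variance arithmetic applies only to a comparison of continuous scores, which is what the sample size addresses.

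A reader might infer more than the article supports:

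- *That the main result is biased by post-randomisation adjustment.* It is not; adjustment is confined to subgroup and additional analyses.
- *That the plan will adjust for bronchopulmonary dysplasia or sepsis while leaving out gestational age.* The phrase names no condition. It cannot be read broadly to take in later morbidities and narrowly to shut out gestational age.
- *That the intervention changes these morbidities.* The article reports such benefits for kangaroo care, which both arms receive, and not for massage.
- *That brain lesions confirmed by 12 months corrected age arose late.* A date of confirmation is not a date of onset.

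**Conclusion.** The point holds in two limited parts.

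First, the score comparison named in the article is valid but less efficient than it need be. Adjustment would be worth about 8 to 28 extra infants (92 − 84 to 112 − 84), provided the baseline variables together correlate 0.3 to 0.5 with the score. The documents give no such figure, so these variables should not be described as strong predictors. The gain in power also depends on the unstated SD: it is useful at the implied 4.9, and modest if the true SD is 10 or 15.

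Second, the wording of the additional analyses permits, but does not prescribe, conditioning on events after randomisation. The distortion ranges from none to about half the 3-point target under assumed values, and it requires the intervention to affect the condition. The main comparison is unaffected. This merits a change of wording; it does not put the design in doubt.

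**What to change.** 1. Pre-specify the main comparison of scores as a linear model on arm, adjusted for a few variables fixed before randomisation, for example gestational age, sex and maternal education. Name them before the data are examined.
2. Keep the unadjusted test as a sensitivity analysis.
3. State that covariates and subgroups in every adjusted analysis are restricted to variables known by 48 hours, and replace the open phrase with a list.
4. Report later neonatal morbidities by arm as outcomes. Any analysis of them as intermediates should be labelled exploratory.

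The cost is analysis wording only. No further infants, visits or measurements are needed. Three covariates reduce the residual degrees of freedom with 84 infants from 84 − 2 = 82 to 84 − 5 = 79, which is negligible.

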### Outcomes

Primary outcome: a global neurodevelopment evaluation will be obtained at 12 to 18 months corrected age for all patients to compare the effect of early systematic intervention independently of formal enriched environments in motor and cognitive aspects. The infants will be evaluated in relation to their motor, and cognitive neurodevelopment using AIMS and Bayley III scales between 12 and 18 months corrected age [14–16].

AIMS (Alberta motor infant scale): a blinded physiotherapist will evaluate the children of both groups between 12 and 18 months with Alberta Infant Motor (AIMS) scale in all eligible patients. The evaluation will be conducted in the presence of parents or caregivers in a safe surface with room for the child move around during the evaluation. The examiner will interact with the child to encourage response, but physical facilitation of movement should be avoided. During the evaluation, they are punctuated behaviors more or less mature within the motor repertoire of the child in each position (supine, prone, sitting and standing). This repertoire is called “motor” window. All items priced within the window motor and the window motor to the previous items are scored. The evaluation of the end, the child will receive a score based on the sum of the items scored on each posture, called raw score. This score will be observed in a standardized chart to find the baby development percentile according to the chronological age or corrected. Percentiles instrument standards are: 5%, 10%, 25%, 50%, 75%. According to this percentile baby’s development can be classified into three categories: normal or typical (percentile> 25%), suspicious (percentile> 5% and ≤ 25%), abnormal or atypical (percentil≤5%) [14].

BSDI-III: *Bayley scales of infant and toddler development third edition*: The Bayley Scales of Infant and Toddler Development, Third Edition, will be used for assessment of neurodevelopment at 12 and 18 months’ corrected age. The scales will be administered at the hospital clinic, on the same day of each follow-up visit, by a psychologist who was blinded to group allocation. Cognitive, motor, and language development will be considered normal if higher than 89; below average if 80 to 89; borderline if 70 to 79; and extremely low if less or equal 69. Examine all the facets of a young child’s development according manual [15].

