Evaluate the impact of the intervention in the neurodevelopment of the children	More strengthened ties to the program start, as measured by PBI resulting in higher scores of attention, care and protection . Number of patients with the Bayley III scale normal for corrected age Number of patients with AIMS scale normal for corrected age. Statistical measures of the differences between the groups (intervention and conventional approaches).	At discharge of neonatal unit (PBI) we will have the first evaluation. After 10 sessions and home visits we will have the follow up evaluations. AIMS and Bayley III Scales at 12 to 18 months corrected age A global neurodevelopment evaluation will be obtained at 12 to 18 months corrected age for all patients.

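### The trial is sized on a 3-point difference in scores, but Table 2 lists only counts of infants classed normal as its Bayley III and AIMS outcomes; the 80% power does not carry over to those counts

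*Protocol article*

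**What the plan says.** The Sample size paragraph works on a continuous quantity. Its conditions begin "For a 5% level of significance and a statistical power of 80" (per cent), and it concludes that "a sample size of 84 patients will be required to detect a 3-point between-group difference in development scores". It then adds 16 infants for loss or death, which gives 100. It states no SD and does not name the scale to which the 3 points belong.

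Table 2, Objective 3, covers the impact of the intervention on neurodevelopment. Its entries for the two developmental scales are "Number of patients with the Bayley III scale normal for corrected age Number of patients with AIMS scale normal for corrected age". The same cell also has an entry on parental bonding and a general one on statistical measures of the difference between the arms.

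The Outcomes section names AIMS and Bayley III together as the primary outcome and describes both scores and categories. For Bayley III, "Cognitive, motor, and language development will be considered normal if higher than 89; below average if 80 to 89". For AIMS, an infant above the 25th percentile is classed as normal. The section does not say which form is compared between arms.

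The Statistical methods paragraph covers both forms. For categories, "Pearson chi-square test will be employed to determine the association between categorical variables, with adjusted residuals in case of statistical significance", with Fisher's exact test also named. For quantitative variables it provides Student's t or Mann–Whitney. Neither kind of test is tied to the primary outcome.

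**The concern.** What was sized and what Table 2 lists as the developmental result are different quantities. A score cut at 89, or at the 25th percentile, keeps only the side of the line on which each infant falls. For roughly normal scores this loses much of the information that the 84 infants were meant to supply. The document gives no calculation for a difference in proportions.

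If the trial were read from the counts, a true effect of the planned size would be missed more often than the stated 20% under that model. A null count comparison could then be taken as evidence that the programme does not work, although the mean scores might have shown a difference. With neither form named as the one that decides, there is also room to choose between them after the results are known.

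**Working it through.** **Inputs from the protocol article.** 5% level, 80% power, 84 infants and a 3-point difference (Sample size); equal arms, 50 each of 100 (Table 2, Objective 1). The 84 is read as a total because 84 + 16 = 100, so there are 42 per arm before loss.

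**Assumptions.** Two-sided test (the side is not stated); normal scores with equal SD in the two arms; the share of controls classed normal is not given, so it is varied.

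**Step 1: the plan's own figure.** Without an SD the 84 cannot be reproduced independently, but the effect that it implies can be solved for.
- Normal approximation: d = (1.960 + 0.842) × √(2/42) = 0.611, so SD = 3/0.611 = 4.91.
- Two-sample t-test with 42 per arm and 80% power: d = 0.619, so SD = 3/0.619 = 4.85.

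The 84 is therefore consistent with a score comparison at about 0.62 SD. At that effect the t-test has 80% power with 42 per arm and 86.5% with 50 per arm.

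**Step 2: the same effect as a normal/not-normal comparison.** If a share p0 of controls is normal, the share in the intervention arm is p1 = Φ(Φ⁻¹(p0) + 0.619). Power is the exact probability of rejection, summed over all pairs of binomial counts, with 42 per arm:

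| Controls normal | Intervention normal | Pearson chi-square | Fisher's exact |
|---|---|---|---|
| 16% | 35% | 54% | 45% |
| 38% (most favourable cut) | 62% | 65% | 57% |
| 50% | 73% | 62% | 53% |
| 69% | 87% | 52% | 42% |
| 84% | 95% | 38% | 23% |

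The most favourable cut lies midway between the two arm means. With d = 0.611 in place of 0.619, its values are 64% and 56%.

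**Step 3: all 100 infants assessed.** With 50 per arm the most favourable cut gives 71% (Pearson) or 64% (Fisher), against 86.5% for the t-test.

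**Step 4: how far this depends on the normal model.** As an illustration, let 10% of infants score 3 SD lower than the rest, and keep the difference at 0.619 of the overall SD. The t-test still has about 80% power with 42 per arm, and the best-placed cut now also gives about 80% by Pearson chi-square. The figures in Steps 2 and 3 are therefore results under a stated model and do not hold for every distribution.

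**The case against.** The strongest reply is that the plan already contains the analysis it was sized for. The Sample size paragraph claims its power only for scores. The Statistical methods provide t and Mann–Whitney tests, and Bayley and AIMS scores are quantitative. Table 2 is introduced as a summary of the project framework, and the cell with the counts also has a general entry that leaves room for comparing scores. Reporting a scale both as a mean and as a share normal is ordinary practice, and a trial need not be powered for each summary. The effect of 0.62 SD is itself back-solved, on a scale that the document does not name.

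Most of this stands, and it limits the point. A reader might infer that the trial's test of impact has at most 65% power, or that its 80% is wrong. The documents support neither reading. The counts are not declared primary, the score comparison keeps its nominal 80% under its own assumptions, and the 65% is not a ceiling for all score distributions or for 100 assessed infants.

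The inconsistency remains. Table 2 is the only place that puts the Bayley III and AIMS results into a countable form, and it names a different quantity from the one that was sized. The Outcomes section does not settle the matter. This is a mismatch between statements on the page, so it is more than detail left to an analysis plan.

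**Conclusion.** The point holds in limited form. The stated 80% covers the comparison of scores and should not be read as covering the numbers classed normal. At the effect implied by 84 infants, the counts have about 65% power by Pearson chi-square at the most favourable cut, a shortfall of about 15 points (80 − 65). With all 100 infants assessed, the figure is about 71%. At the less favourable cuts computed, with 16% to 84% of controls normal, it is about 38% to 62%. Fisher's exact test is lower throughout.

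This rests on a back-solved effect of about 0.62 SD, normal scores with equal SD, a two-sided 5% level and equal arms. If the true SD is larger than about 4.9, 3 points is a smaller standardised effect and both analyses lose power. The matter is worth correcting because the correction is cheap. It does not show that the planned score analysis is inadequate.

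**What to change.** - In Table 2, Objective 3, and in the Outcomes section, name the between-group difference in mean score, with its 95% confidence interval, as the measure of impact, and say to which scale the 3 points refer.
- Keep the numbers of infants classed normal on Bayley III and AIMS as secondary outcomes.
- In the Sample size paragraph, state that the 80% power refers to the score comparison only.

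This changes wording in three places. It needs no further infants, visits or data, because the scores are already collected to form the categories. The cost is that the share normal, which is easier to communicate, becomes secondary.
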